#### **Ectopic fat depots**

Abdominal subcutaneous and intermuscular adipose tissue, as well as hepatic fat fraction will be quantified by magnetic resonance imaging (Siemens 3T Magnetom Vida). Semiautomatic software for tissue segmentation will be used to calculate visceral, subcutaneous, and intermuscular abdominal adipose tissue variables in all 3D abdominal volume: volume, cross-sectional area at selected levels, and mean/median fat fraction. These image markers will be derived from a standard 6 echo Dixon series. At L3 and L5 levels, we will obtain these image markers: cross-sectional area, muscular tissue, and intramuscular fat fraction. We will also quantify with a 6 echoes Dixon series, the fat fraction in all lumbar vertebral bodies, from a mid-sagittal image.

The segmentation of these areas will be manually edited. Lastly, we will measure image markers from mid-thigh. Again, using a 6 echoes Dixon series, we will obtain cross-sectional area, muscular tissue, intermuscular adipose tissue, fat fraction, subcutaneous adipose tissue, and bone marrow fat fraction. The segmentation for all these structures will be done with a semiautomatic proprietary algorithm.

## **Cardiometabolic risk factors**

Fasting blood samples will be collected to analyze:

- Glucose (AU5800 automated analyzer, Beckman Coulter Inc., CA, USA), insulin (UniCel DxI 800 access immunoassay system, Beckman Coulter Inc., CA, USA), and HbA1c (HA-8180V® analyzer, A Menarini Diagnostics, Firenze, Italy). Simple insulin resistance surrogates such as the HOMA-IR and the quantitative insulin-sensitivity check index (QUICKI) will be calculated.
- Lipid profile, including total cholesterol, high-density lipoprotein cholesterol, triglycerides, apolipoprotein A1 and B, will be measured using a AU5800 automated analyzer, Beckman Coulter Inc., CA, USA. Low-density lipoprotein cholesterol will be calculated using a previously validated equation [21].
- Bone metabolism profile, including Vitamin D (measured using a UniCel DxI 800 access immunoassay system, Beckman Coulter Inc., CA, USA), alkaline phosphatase (measured by Liaison, Diasorin, Saluggia VC, Italy), and calcium (measured using a AU5800 automated analyzer, Beckman Coulter Inc., CA, USA).
- Liver and kidney function markers, including alanine transaminase, gamma-glutamyl transferase, bilirubin, creatinine (measured using a AU5800 automated analyzer, Beckman Coulter Inc., CA, USA), and estimated glomerular filtration rate.
- Steroid hormones, including estradiol, progesterone, and testosterone (measured using a UniCel DxI 800 access immunoassay system, Beckman Coulter Inc., CA, USA).
- Thyroid hormones, including thyrotropin, thyroxine, and triiodothyronine (measured using a UniCel DxI 800 access immunoassay system, Beckman Coulter Inc., CA, USA).

- Blood count and biochemistry markers, including iron, ferritin, and folic acid (measured using a AU5800 automated analyzer, Beckman Coulter Inc., CA, USA).

Blood samples will be also stored at -80°C for future analysis. The systolic and diastolic blood pressure will be measured with an automatic monitor (M3-Comfort, Omron Healthcare Europe B.V. Hoofddorp, The Netherlands, in both Granada and Pamplona) following the 2021 European Society of Hypertension practice guidelines [22].

### **Glycemic control**

Participants will wear a continuous glucose monitoring (CGM) device (FreeStyle LibrePro, Abbott, in Granada and FreeStyle 2, Abbott, in Pamplona) during two weeks before the intervention (lead-in period) and during the last two weeks of the intervention. From the CGM data several variables of glycemic control will be calculated according to the last international consensus statement [23]. Data from the CGM will be processed using an R code located in <https://github.com/DIVA-soft/CGManalyzer>. Concurrently, sleep physical activity levels will be objectively measured using accelerometers.

### **Sleep and physical activity assessment**

Sleep, chronotype, and physical activity will be subjectively assessed using validated questionnaires including the Pittsburgh Sleep Quality Index (PSQI), Munich Chronotype Questionnaire (MCTQ), Horne y Östberg (MEQ-SA), and the International physical activity questionnaire (IPAQ). Sleep and physical activity levels will be also objectively assessed using accelerometers. Specifically, participants will wear a triaxial accelerometer (ActiGraph GT3X+, Pensacola, FL, USA, in both Granada and Pamplona) on the non-dominant wrist during two weeks before the intervention (lead-in period) and during the last two weeks of the intervention. The data will be processed in the GGIR R package (version 2.10-3). Accelerometer and CGM data will be time-matched using the experimental tool that can be accessed in <https://github.com/DIVA-soft/GGIRmatcher>.

## **Gut microbiota**

Faecal samples will be collected at baseline and during the last two weeks of the intervention to extract genomic DNA and thereafter, to perform the metagenomics analysis (16S rRNA gene amplicon sequencing – shotgun methodology will be considered pending the final budget) to obtain a complete description of gut microbioma diversity and composition. Besides, a faecal metabolomic fingerprint analysis will be carried out in order to establish the metabolic profile in the different groups of patients by liquid chromatography method coupled to mass spectrometry (LC-MS).

## **Psychosocial assessment**

Participants will complete validated questionnaires regarding several psychosocial dimensions: Beck Depression Inventory Fast Screen (BDI-FS), Perceived Stress Scale (PSS), and State-Trait Anxiety Inventory (STAI).

## **Eating behaviour assessment**

Eating behaviour will be assessed using validated questionnaires: Food Craving Inventory (FCI) and the Adult Eating Behavior Questionnaire (AEBQ).

## **Dietary habits assessment**

Participants will complete a validated questionnaire to assess their adherence to the Mediterranean dietary pattern [24]. Moreover, three non-consecutive 24h dietary recalls (two of working days and one of non-working day) will be recorded in a face-to-face or telephone interview by qualified and trained research dietitians.

## **Quality of life**

Quality of life will be evaluated using the EuroQol 5 dimensions 5 levels (EQ-5D-5L), Rand Short Form 36 (SF-36), an adverse events questionnaire and menstrual questionnaire.

| Outcomes                                 | Baseline | 12-week post intervention |  |
|------------------------------------------|----------|---------------------------|--|
| Primary outcome                   |          |                           |  |
| Visceral adipose tissue (i.e., MRI)      | ✓        | ✓                         |  |
| Secondary outcomes                |          |                           |  |
| Body weight and anthropometry            | ✓        | ✓                         |  |
| Body composition (i.e., DXA)             | ✓        | ✓                         |  |
| Ectopic fat depots (i.e., MRI)           | ✓        | ✓                         |  |
| Cardiometabolic risk factors             | ✓        | ✓                         |  |
| Interstitial glycemic traits (i.e., CGM) | ✓        | ✓ *                       |  |
| Gut microbiota                           | ✓        | ✓ *                       |  |
| Sleep and physical activity (i.e., ACC)  | ✓        | ✓ *                       |  |
| Psychosocial assessment                  | ✓        | ✓                         |  |
| Eating behaviour assessment              | ✓        | ✓                         |  |
| Dietary habits                           | ✓        | ✓                         |  |
| Quality of life                          | ✓        | ✓                         |  |

sment will be conducted during the last two weeks of the intervention. Abbreviations: MRI, magnetic resonance imaging; DXA, dual-energy X-ray absorptiometry; CGM, continuous-glucose monitoring; ACC, accelerometry.

### 3.8 Time-restricted eating intervention

Participants will be randomly assigned to one of the following four groups:

- UC: Participants in the UC group will continue with their dietary eating time schedule and will receive, as well as the participants in the TRE groups, an educational program for weight management and cardiovascular health promotion based on Mediterranean dietary pattern [25] and physical activity recommendations from the World Health Organization [26].
- Early TRE: Participants will select an early 8h eating window (i.e., starting not later than 10:00) before the intervention, and will maintain the same 8h eating window during the 12-week intervention.
- Late TRE: Participants will select a late 8h eating window (i.e., starting not before 13:00) before the intervention, and will maintain the same 8h eating window during the 12-week intervention.
- Self-selected TRE: Participants will select their preferred 8h eating window before the intervention and will maintain the same 8h eating window during the 12-week intervention.

No calorie-containing food or beverage intake will be allowed outside the eating window for the three TRE groups. Only water, coffee, and tea without sugar or artificial sweeteners will be allowed outside the eating window for the TRE groups. Participants in the TRE groups will be instructed to perform the TRE intervention every day of the week (i.e., seven days).

### **3.9 Usual-care intervention**

Intervention meetings for all groups will take place every two weeks by experienced nutritionists. It will be voluntary, but attendance to the meetings will be recorded. There will be 6 topics to be addressed in each intervention meeting: (i) healthy lifestyle based on Mediterranean dietary pattern and physical activity recommendations; (ii) organization and planning of food intake; (iii) control of hunger and satiety; (iv) nutritional labelling; (v) nutritional myths; and (vi) healthy snacks. After each meeting, experienced research nutritionists will answer the doubts/questions of the participants.

### **3.10 Assessment of adherence and adverse events**

Every day during the 12-week intervention, all participants will record their time of sleep, eating, and any potential adverse event using a mobile phone app (EXTREME: com.nnbi.app\_extreme, NNBi2020 S.L., Navarra, Spain). Participants will record the exact time of initiating their first meal and concluding their last meal over the 12-week intervention period. If the records indicate that participants eat within their allocated window of 8h ( $\pm 30$  minutes) that day will be labelled as "adherent".

The Study Coordinators will record the frequency of adverse events and report them to the Principal Investigators weekly. If a serious adverse event or unanticipated problem is reported, the Study Coordinators will immediately notify the Principal Investigators and Medical Monitor, who will determine if it is necessary to inform the ethics committee and determine the appropriate course of action to address the event.

### **3.11 Participants retention**

Every effort will be made by the Principal Investigators and study team to ensure participants complete each study visit and the study overall. We will use the following strategies to help to maximize retention and minimize loss to follow-up:

- Following a proactive plan for retention, building participant relations and participant satisfaction. Including asking participants how they are feeling during the intervention meetings.
- Giving participants and their families the opportunity to ask questions and express concerns pertaining to their condition throughout the study.
- Enhancing participant's understanding of the study's objectives and the protocol by reminding the participant of the study aim during study visits or having question and answer sessions after each visit, if needed.
- Assessing each participant's drop-out potential and intervening as needed to keep participants interested in continuing to participate.

### 3.12 Feasibility

We will assess the feasibility of the intervention through various measures, including:

- Adherence monitoring: Participants will use a custom mobile phone app (EXTREME: com.nnbi.app\_extreme, NNBi2020 S.L., Navarra, Spain). developed specifically for this study to track and record their daily eating and sleep times. This data will provide insights into their adherence to the prescribed eating window.
- Acceptability: During the biweekly educational sessions, we will gather feedback from participants who are undergoing the TRE intervention. This feedback will help us to understand their experiences and perceptions of the intervention, providing valuable insights into the acceptance and integrity of the intervention in their everyday lives. Participants will also have the opportunity to report any adverse events related to the intervention.
- Adverse effects and health-related questionnaires: Participants will have the ability to report any adverse effects they experience on a daily basis through the mobile phone app (EXTREME: com.nnbi.app\_extreme, NNBi2020 S.L., Navarra, Spain). Additionally, they will complete validated questionnaires that assess gastrointestinal and autonomic symptoms, well-being, eating behaviour, sleep quality, stress levels, mood, anxiety, and depression. These questionnaires will provide valuable information on any potential adverse effects and overall health-related outcomes.

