## **2. AIMS**

The overall aim of the present study is to investigate the efficacy and feasibility of three different 8h TRE schedules (i.e., early, late, and self-selected) compared to each other and to a usual-care (UC) intervention over 12 weeks on VAT, body composition and cardiometabolic health in adults with overweight/obesity.

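### Acceptability of the TRE schedules is asked about only at voluntary sessions, so participants who stay away or leave are under-represented and acceptability may be overstated

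*Combined protocol and SAP*

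**What the plan says.** Section 2 makes feasibility part of the main question: "The overall aim of the present study is to investigate the efficacy and feasibility of three different 8h TRE schedules". Section 1 argues that letting people choose their own window may help adherence and acceptability, which is the rationale for the self-selected arm.

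Section 3.12 then lists three kinds of feasibility measure:

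- **Adherence**, from eating times entered in the EXTREME app. Section 3.10 asks for daily entries and sets the rule for a day to count: "If the records indicate that participants eat within their allocated window of 8h", with a tolerance of 30 minutes either way.
- **Acceptability**: "During the biweekly educational sessions, we will gather feedback from participants who are undergoing the TRE intervention". No instrument is named, and no route is given for people who are not at a session.
- **Adverse effects and questionnaires**. Adverse effects are reported daily in the app. For the rest: "Additionally, they will complete validated questionnaires that assess gastrointestinal and autonomic symptoms, well-being, eating behaviour, sleep quality, stress levels, mood, anxiety, and depression".

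Section 3.9 sets the sessions every two weeks and says of attendance: "It will be voluntary, but attendance to the meetings will be recorded". Table 2 and section 3.7 list no acceptability item at any time point. Section 4.3 describes the analysis of primary and secondary outcomes and gives none for feasibility.

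**The concern.** A participant who finds the eating window hard to live with may well be less inclined to come to an optional meeting about it, and one who has withdrawn is unlikely to come at all. If opinions are collected only in that room, they come from a self-selected group, and the selection may depend on the thing being measured.

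Two conclusions are at stake. One is the overall statement about how acceptable 8-hour TRE is. The other is the comparison of early, late and self-selected windows: if one schedule is harder and loses more of its dissatisfied participants from the sessions, the feedback that remains may look more alike across arms than the arms really are. Part of the case for the self-selected arm rests on that comparison.

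**Working it through.** The plan states no feasibility target, rate or threshold, so there is no figure to reproduce. The check has two parts: which stated measure could reach the missing people, and how large the effect could be under openly assumed rates.

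**1. Does any other stated measure fill the gap?**

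| Source in the plan | Depends on attending sessions? | Described as asking whether the window is acceptable? | Stated withdrawal assessment? |
|---|---|---|---|
| Session feedback (3.12) | Yes | Yes | No |
| App adverse-effect reports (3.10, 3.12) | No | No | No |
| Questionnaires (3.7, 3.12, Table 2) | No | No | No |
| Attendance record (3.9) | Not applicable | No | No |
| Retention contacts (3.11) | Partly | No | No |

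No row other than the first is described as measuring acceptability, and no row has an exit measure.

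**2. Size of the selection effect.** Let *a* be the share of TRE participants who are ever heard, *p1* the share of them who find the window acceptable, and *p0* the same share among those not heard.

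- Reported = *p1*. True = *a·p1* + (1 − *a*)·*p0*. Overstatement = (1 − *a*)(*p1* − *p0*).
- Assume *a* = 60%, *p1* = 85%, *p0* = 50%. True = 0.60 × 0.85 + 0.40 × 0.50 = 71%, against 85% reported: 14 points.
- If *p0* = *p1*, the overstatement is 0 whatever *a* is.

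**3. How many are never heard?** Meetings every two weeks for 12 weeks give 12 / 2 = 6 meetings. With an assumed 60% attendance per meeting, the share missing all six is:

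- 0.4^6 = 0.4% if attendance is independent from meeting to meeting;
- 40% if the same people are always absent.

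With the approval rates of step 2, the overstatement runs from 0.004 × 35 ≈ 0.1 points to 0.40 × 35 = 14 points. The low end counts a single early comment as being heard; it says nothing of the person's view at week 12.

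**4. Dropout at the plan's own allowance.** Section 4.2 allows for about 20% dropout in groups of about 52, that is 0.20 × 52 ≈ 10 per arm. Suppose dropouts give no feedback, everyone else does, and 85% of those find the window acceptable (assumed). The reported figure is 85%. The true figure lies between 0.80 × 0.85 = 68% and 0.68 + 0.20 = 88%.

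**5. Between schedules.** Keep 85% and 50%, and let 80% be heard in an easier arm and 50% in a harder one. The true figures are 0.80 × 0.85 + 0.20 × 0.50 = 78% and 0.50 × 0.85 + 0.50 × 0.50 = 67.5%, a gap of 10.5 points. Both arms report 85%, but only because approval among those heard was set equal in the two arms. The example shows that blurring can happen, not that it will.

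**6. Adherence, a secondary matter.** There are 12 × 7 = 84 possible days. Section 3.10 gives neither a denominator nor a rule for an unlogged day. Assume 80% of days are logged and 85% of those are adherent. The logged-days rate is 85%; the all-days rate with unlogged days scored as not adherent is 0.80 × 0.85 = 68%. The true rate is 0.68 + 0.20 × *A0*, where *A0* is adherence on unlogged days:

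| *A0* (assumed) | True | Error of logged-days rate | Error of all-days rate |
|---|---|---|---|
| 85% | 85% | 0 | −17 points |
| 50% | 78% | +7 | −10 |
| 25% | 73% | +12 | −5 |
| 0% | 68% | +17 | 0 |

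Neither rate is right in general.

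**The case against.** The strongest reply is that the plan already has several ways of seeing poor acceptability. Attendance is recorded and can be shown by arm. Adverse effects come in daily through the app, and the eating-behaviour, psychosocial and quality-of-life assessments at 12 weeks do not depend on the sessions. Participants can raise concerns throughout (3.11), and the attrition model in 4.3 includes allocation group. Dropout that differs by arm would itself be evidence on feasibility. With about six meetings, many participants who struggle may be heard at least once. The feedback is described as a way to understand experience, not as a percentage to be reported.

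Much of this stands. It limits the likely size and means the problem would not be wholly invisible. It does not close the gap: an attendance count shows how many people were not asked, not what they would have said, and the other instruments are not described as asking about the window. Section 3.12 introduces its list as non-exhaustive, but a measure that is not specified cannot be relied on.

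A reader might go further and infer that the least compliant participants disappear from both acceptability and adherence, so that feasibility is overstated and the difference between schedules hidden. The documents do not support that. They give no attendance or logging rates and do not link either to compliance. Section 3.10 does not exclude unlogged days; read literally, such a day simply fails to earn the adherent label, which would lower a rate taken over all days. Nor can it be said that non-attenders are never asked, since a participant would have to miss every meeting.

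**Conclusion.** The point holds for acceptability. A component of the stated aim has one named data source, that source is optional, and no week-12 or exit measure backs it up. Acceptability may therefore be overstated and differences between schedules blurred. The size cannot be determined from the documents. The illustrations run from no bias, when those not heard think as the others do, to 14 points at the assumed 60%, 85% and 50%. Every one of these inputs except the six meetings, the group size and the 20% dropout allowance is an assumption.

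For adherence the finding is only that the denominator and the handling of unlogged days are undefined. The direction of any error depends on choices the plan has not made.

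The primary VAT intention-to-treat analysis does not use these measures. The per-protocol analysis in 4.3 could be touched if its set is defined by app adherence, which the plan does not say.

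**What to change.** **In 3.12 (main change).** Collect a short, fixed set of acceptability items from every randomized TRE participant at the 12-week assessment and, where possible, at withdrawal, through the EXTREME app or REDCap, regardless of session attendance. Add the items to Table 2. Report the results by arm, with response rates and session attendance beside them, and treat session feedback as supplementary.

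**In 3.10 (clarification).** Report logging completeness by arm, and show adherence both on logged days and over all 84 intervention days, without presuming which is correct.

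**Cost.** One short extra form in systems the trial already uses, and a few lines of text. The exit form must be optional, since section 5.2 allows withdrawal without explanation, so some who leave will still not respond. The response rate by arm will show how much of the gap remains.

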### **3.13 Data management**

The majority of data will be recorded directly into REDCap, which is a secure web-based platform for building and managing online research-related databases and surveys. Any data not recorded in REDCap will be stored securely on university computers under strict access control to ensure confidentiality and data integrity. To ensure data quality and integrity, we will perform regular data quality control checks that may identify potential data anomalies, such as missing data or forms, out-of-range or erroneous data, inconsistent and illogical dates over time, data inconsistency across forms and visits, and incomplete fields on completed forms without a reason for missing data provided. Any identified issues will be reviewed and resolved by the research team promptly.

